### Criteria for discontinuing or modifying allocated interventions {11b}

This study is designed to cause minimal harm to the research participants while producing the most benefit. Topics discussing with the diabetes educator and CHW may be related to sensitive topics such as their current or past medical conditions, including those related to diabetes and weight, specific laboratory results and lifestyle choices such as eating habits and physical activity. All staff are trained to identify and support participants who may be uncomfortable. At the beginning of each DSMT sessions, the diabetes educator will inform participants that they are free to leave at any time if they are uncomfortable. This will not jeopardize their participation in the study nor will it impact their relationship with Sinai Chicago as a patient. All adverse reactions will be reported to the patient’s primary clinical team and the IRB. One of the PIs (JJ) leads weekly meetings with the implementation team which will be the first-line opportunity to identify and discuss any concerns across the participant. The PIs meeting biweekly to discuss updates and challenges, and the Subject Matter Expert (SME) Committee, described in more detail below, consists of a team of diabetes and community health specialist who will review cases as needed to determine any necessary modifications.

### Strategies to improve adherence to interventions {11c}

Participants randomized to the DSMT study arm will receive a call or text message from the diabetes educator prior to each session to remind them of the class. For participants who are not able to join one of their regularly scheduled sessions, a make-up class will be offered to maximize adherence. Participants randomized to the RGM study arm will receive a call or text message from a research staff member every 2 months to provide technical assistance and encourage engagement with the application. Finally, participants randomized to the CHW study arm will receive a call or text message from the CHW prior to each one-on-one visit. We will measure intervention adherence using attendance (number of DSMT sessions attended), RGM utilization (number of blood glucose readings uploaded to Glooko and number of syncs to Sinai’s medical record system), and adherence with CHW enhancements: (1) completing an initial education session, (2) completing a SDoH screener, (3) connecting with the CHW via phone or in person at least three times over 6 months.

### Relevant concomitant care permitted or prohibited during the trial {11d}

All study participants will be able to seek standard of care for diabetes management during the study period. To prevent contamination, individuals who are randomly assigned to the DSMT study arm will not be provided with a Glooko license until the study is complete. Individuals in the RGM study arm will not be offered specialized diabetes education from a diabetes educator until the study is complete. Individuals will only be offered resources as it pertains to the standard of care.

### Provisions for post-trial care {30}

Upon completion of the trial, all study participants will be offered a Glooko license for RGM utilization to support ongoing monitoring of their blood glucose levels. Individuals will also be provided with diabetes education as necessary and as covered by their insurance. The Centers for Medicare and Medicaid cover up to 10 h of diabetes education sessions per year. As needed, patients will also be offered an appointment with a CHW employed by the Center to support any social needs.

### Outcomes {12}

The primary outcome of interest is HbA1c, a clinical measure of diabetes management. We will measure the change in HbA1c from baseline (must be from within the 90 days prior to enrollment) to the 12-month study end point. HbA1c will be measured every 6 months, with the first 6-month measurement serving as our tailoring variable for the SMART. Patients with an HbA1c reduction of at least one percentage point will be considered responders [29].

The secondary outcomes of interest are implementation outcomes and patient-centeredness. The implementation outcomes that will be measured include appropriateness, fidelity, sustainability, and patient-centeredness. We define appropriateness as the perceived fit or compatibility with the patient population, staff, and organization; fidelity as the degree to which the intervention is implemented as intended; and sustainability as the extent to which the treatment is sustained or maintained. Patient-centeredness will be measured using the six dimensions defined by the Institute of Medicine. See Table 2 for a full list of outcomes measures and data sources.

**Table 2 Tab2:** Outcomes and data sources

**Domain**	**Specific measurement**	**Specific metric**	**Method of aggregation**	**Timepoint**	**Data source**
Clinical Effectiveness	HbA1c	Change from baseline	Proportion of participants with a decrease of at least 1 percentage point	6 and 12 months post enrollment	EMR
Fidelity	Active RGM Usage	Value at intervention completion	Binary value (Y/N: at least one upload of data within a 30-day period and at least 16 blood glucose entries within a 30-day period)	6 months after enrollment or rerandomization^a^	Glooko Reports
	DSMT attendance	Value at intervention completion	Binary value (Y/N: attended at least three of four sessions)	6 months after enrollment or rerandomization^a^	DSMT Attendance Sheets
	Adherence to CHW engagement	Value at intervention completion	Binary value (Y/N: completed initial education session, SDoH screener, and at least three meetings with CHW)	6 months after enrollment or rerandomization^a^	CHW Log Sheet
Appropriateness	Perceived appropriateness, fit, and compatibility with patient population and organization from the perspectives of Center staff and patients	Qualitative self-reported experiences	N/A	Between 3 and 6 months after enrollment or rerandomization^a^	Center Staff Interviews Patient Focus Group Discussions
Sustainability	Short Form-Diabetes Empowerment Scale (SF-DES)	Change from baseline	Mean	6 and 12 months post enrollment	RedCAP Study Database
	Problem Areas in Diabetes (PAID) Survey	Change from baseline	Mean	6 and 12 months post enrollment	RedCAP Study Database
Patient-Centeredness	Respect for patients’ values, preferences, and expressed needs Coordinated and integrated Provide Information, communication, and education Ensure physical comfort Provide emotional support Involve family and friends	Qualitative self-reported experiences	N/A	Between 3 and 6 months after enrollment or rerandomization^a^	Patient Focus Group Discussions
Covariates	Race/ethnicity, Age, Sex, Zip code, Insurance status	Value	Distribution across categories	Baseline	EMR RedCAP Study Database

*RGM* remote glucose monitoring, *DSMT* diabetes self-management training, *CHW* community health worker, *EMR* electronic medical record, *SDOH* social determinants of health, *N/A* not applicable, qualitative measure

^a^Depending on initial and/or secondary if participant was assigned to RGM at their initial or rerandomization point

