### Eligibility criteria {10}

Eligibility criteria for each study component (SMART, participant focus group discussions, and staff interviews) are described in Table 1.

**Table 1 Tab1:** IDEA study eligibility criteria

Study component	Inclusion criteria	Exclusion criteria
SMART	• Diagnosed with type 1 or type 2 diabetes • 18 years of age or older • Able to provide informed consent • African American/Black or Latine • HbA1c level ≥ 7% measured within 365 days prior to study enrollment • Have a smartphone compatible with the Glooko RGM application [20] • Completed at least one appointment at the Center since the Center opened in 2020 • Fluent in English or Spanish	• Have an activated Power of Attorney • Diagnosed with Stage V renal disease or undergoing dialysis • Diagnosed with a severe form of cardiovascular disease • Diagnosed with gestational diabetes only (without type 1 or type 2) • Diagnosed with any severe form of mental disorder including schizophrenia, bipolar disorder, or severe depression • Pregnant • Diagnosed with Alzheimer’s disease or dementia • Already an active user of RGM • Actively working with a CHW for their diabetes • Planning to travel outside of the Chicagoland area for more than three months in the year following study enrollment • Use a continuous glucose monitor that is incompatible with the Glooko RGM application
Participant Focus Group Discussions	• Meet all eligibility for SMART component of study • Completed at least 3 months of their assigned SMART study condition	None
Center Staff Interviews	• Employed by the Center during the study period • 18 years of age or older • Able to provide informed consent • Fluent in English or Spanish	None

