### Sample size {14}

The sample size calculation, performed using G*Power (version 3.1), is based on the primary outcome of HbA1c over the 12-month study period, with the primary predictor being the six treatment conditions taken over the course of the study. The Null (H0) and Alternative (H1) Hypotheses are H0: There is no difference in the mean change in HbA1c among the six treatment groups, and H1: There is a significant difference in the mean change in HbA1c among the six treatment groups. The analysis assumes a significance level of 5%, 80% power, six treatment groups, equal group allocation, and a medium effect size of *f* = 0.25. The effect size of *f* = 0.25 was selected based on Cohen’s conventions for effect sizes in behavioral sciences, where 0.10 represents a small effect, 0.25 represents a medium effect, and 0.40 represents a large effect. A medium effect size is considered appropriate for this study, as it balances the detection of meaningful clinical differences with practical sample size considerations. Previous studies on diabetes management interventions such as DSMT and RGM have reported effect sizes in this range, indicating that a medium effect size is a reasonable expectation for interventions aimed at reducing HbA1c [13, 25].

The sample size estimation properly accounted for the multiple groups and comparisons inherent in the SMART design. Specifically, we conducted the sample size estimation for detecting a difference in HbA1c change across the six treatment groups, using an ANOVA framework, which inherently accounts for multiple comparisons. To ensure robustness and accommodate potential dropouts, we inflated the sample size by 20%. Thus, the minimum required sample size is 216 patients, and to account for an anticipated dropout rate, we aim to recruit 270 patients. This approach ensures that the study is adequately powered to detect significant differences across all treatment conditions, providing a solid basis for our subsequent analyses.

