## Assignment of interventions: allocation

### Sequence generation {16a}

The sequence of study arm assignment will be done using a modified version of the sequentially numbered, opaque sealed envelopes (SNOSE) [30]. In order to empower study participants to ensure they feel like part of the study and have a sense of autonomy, we created randomization envelopes that participants will be able to choose from. Following guidance from Doig & Simpson, we took several steps to design and create randomization allocation envelopes that will be concealed from the participant and the researcher. We developed a detailed operating procedure and provided this to a staff member who is unfamiliar with the research study. For the first randomization, the staff member printed out 150 pieces of paper that say “DSMT” and 150 pieces of paper that say “RGM”. Starting with the “RGM” paper, they folded each one and put it into a completely opaque security envelope. Each envelope was sealed and the staff member wrote their initials, in pen, on the top of the envelope seal. The same steps were repeated for the DSMT paper. Once all 300 envelopes were created, the staff member created two boxes of envelopes, stratified by recruitment site. For the first box, for patients recruited from Mount Sinai Hospital, the staff member selected 75 RGM envelopes and 75 DSMT envelopes. These were shuffled thoroughly and placed in the box marked “MSH”. For the second box, for patients recruited from Holy Cross Hospital, the staff member shuffled the remaining 75 RGM envelopes and 75 DSMT envelopes and placed them in the box marked “HCH”. These boxes and their sealed envelopes were placed in a study team member’s locked office to prepare for recruitment.

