### Methods in analysis to handle protocol non-adherence and any statistical methods to handle missing data {20c}

In order to address potential issues related to protocol non-adherence in our SMART design, we will employ specialized analytical methods that are tailored to adaptive interventions. Unlike traditional clinical trials where intention-to-treat (ITT) and per-protocol (PP) analyses are commonly used, our study’s design necessitates a different approach due to the planned adaptability of the interventions based on participants’ responses.

We will utilize Q-learning and g-estimation strategies to analyze the primary and secondary outcomes. These methods are specifically designed for adaptive interventions and will allow us to estimate the causal effects of the different sequences of treatments while accounting for the adaptive nature of the intervention. By employing these methods, we aim to obtain unbiased estimates of treatment effects, even in the presence of protocol non-adherence due to the adaptive design.

To handle missing data, we will implement multiple imputation (MI) techniques using a fully conditional specification (FCS) approach, also known as multiple imputation by chained equations (MICE). The imputation model will include variables predictive of the missing values and outcomes, such as baseline HbA1c, age, sex, race/ethnicity, intervention group, and socioeconomic status. Imputation will be performed separately within each treatment arm to account for differences in data distributions, generating 20 imputed datasets to ensure stability and reliability. Each imputed dataset will be analyzed using the specified statistical models for primary and secondary outcomes, including one-way ANOVA, linear regression models, and Q-learning algorithms. The results from the imputed datasets will be combined using Rubin’s rules to produce valid statistical inferences accounting for the uncertainty due to missing data.

To validate the imputation model, we will compare the distribution of imputed values with observed values. Sensitivity analyses will be conducted to assess the robustness of our findings under different missing data mechanisms, comparing results from multiple imputation with those obtained from complete-case analyses and other missing data approaches. This approach aims to ensure accurate and reliable estimates, maintaining the validity of our study’s findings.

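### Recruitment site stratifies the first randomisation but is not named in the covariate row or the imputation variables, and the one-way ANOVA cannot carry it; the cost is modest precision

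*Protocol article*

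**What the plan says.** **Design.** Sequence generation {16a} states that for the first randomisation "the staff member created two boxes of envelopes, stratified by recruitment site", each box holding 75 envelopes per arm. The second-stage boxes are stratified by initial treatment only, so site is not controlled there.

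**Covariates.** The covariate row of Table 2 (Outcomes {12}) reads "Race/ethnicity, Age, Sex, Zip code, Insurance status". Neither recruitment site nor diabetes type appears, although the eligibility table admits both types: "Diagnosed with type 1 or type 2 diabetes".

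**Models.** Statistical methods {20a} labels as primary a linear regression adjusted for baseline characteristics that it does not enumerate. It then compares the six conditions by one-way ANOVA with Tukey comparisons, or by Kruskal-Wallis and Dunn tests if the data are not normal. None of these has a site term. Further regression covariates are given as examples, among them baseline and 6-month HbA1c. Inverse probability weighting is a sensitivity analysis.

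**Imputation.** Section {20c} gives its variables as examples: "such as baseline HbA1c, age, sex, race/ethnicity, intervention group, and socioeconomic status".

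**Data flow.** Under Concealment mechanism {16b} the first digit of the participant number is the site. Under Who will be blinded {17a} the statistician receives a different identifier, because the participant number reveals the arm.

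**The concern.** A factor used to restrict randomisation should normally be in the model. Stratifying by site makes the arms alike in site mix. A model without site still counts between-site variation as error, so its standard errors are somewhat too large and the balance bought by stratifying is not used. At the second stage site is balanced only by chance, and a comparison without covariates cannot correct for it. Zip code does not replace clinic site, because the two boxes are defined by hospital.

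There is also a practical side. The statistician's identifier does not carry site, so if site is not listed as an analysis variable it may not reach the analysis dataset. What is at stake is precision and a covariate choice settled in advance, not bias in the treatment comparison.

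**Working it through.** **1. The plan's own figure.** Sample size {14} states: "The analysis assumes a significance level of 5%, 80% power, six treatment groups, equal group allocation, and a medium effect size of" f = 0.25. For a one-way ANOVA with k = 6, the noncentrality is N·f² = 216 × 0.0625 = 13.5 on 5 and 210 degrees of freedom.
- The smallest N with 80% power is 211 (power 0.800). Six equal groups of 36 give 216 (power 0.811).
- With 20% dropout, 216/(1 − 0.20) = 270.

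Both stated figures are reproduced. The calculation contains no covariates.

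**2. Variance attributable to site (assumption).** The documents give no site effect and no SD. Take equal sites (p = 0.5) and a site difference d in 12-month HbA1c change of 0.2 to 0.5 within-site SD.
- Share of variance = p(1−p)d² / (1 + p(1−p)d²).
- d = 0.2: 0.25 × 0.04 = 0.01, and 0.01/1.01 = 1.0%.
- d = 0.5: 0.25 × 0.25 = 0.0625, and 0.0625/1.0625 = 5.9%.
- Standard errors fall by the factor √(1 − share): √0.990 = 0.995 and √0.941 = 0.970, that is 0.5% to 3%.

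**3. Type I error of the first-stage two-arm test without site.** With exact balance within sites, the error rate is 2·(1 − Φ(1.96·√(1 + 0.25d²))).
- d = 0.2: 1.96 × √1.01 = 1.970, giving 4.9%.
- d = 0.5: 1.96 × √1.0625 = 2.020, giving 4.3%.

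Both are below 5%, so the test is mildly conservative.

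**4. Simulation.** Each setting used 4,000 trials, with 135 patients per site drawn from 75/75 boxes and an assumed one-third of patients responding. The Monte Carlo standard error is about 0.0035.

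| Site share of variance | Two-arm, no site | Two-arm, with site | Six conditions, no site | Six conditions, with site |
|---|---|---|---|---|
| 0 | 0.046 | 0.047 | 0.052 | 0.052 |
| 2% | 0.055 | 0.057 | 0.045 | 0.046 |
| 5% | 0.051 | 0.056 | 0.049 | 0.051 |
| 10% | 0.040 | 0.051 | 0.053 | 0.055 |

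The six-condition test shows no inflation without site. The two-arm test falls clearly below nominal only at the 10% share.

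**5. Power.** Replace f² by f²/(1 − R²), allowing two degrees of freedom (site and, optionally, diabetes type). At N = 216, power moves from 0.811 to 0.816 at R² = 1%, 0.820 at 2%, 0.834 at 5% and 0.856 at 10%.

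**6. Second-stage imbalance (assumption).** With 270/2 = 135 patients per first-stage arm and one-third responding, 90 are re-randomised, about 45 per option.
- With equal sites, the SD of the difference in site share between two options is √(2 × 0.25/45) = 0.105, about 10 percentage points.
- With d = 0.5, a one-SD imbalance shifts a contrast by 0.105 × 0.5 ≈ 0.05 SD.

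This is chance variation already reflected in the unadjusted standard error. Adjustment would remove it.

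**7. Diabetes type (assumption).** With 5% to 20% type 1 and a 0.3 to 0.5 SD difference, the formula in step 2 gives 0.4% (0.0475 × 0.09 = 0.0043) to 3.9% (0.16 × 0.25 = 0.04; 0.04/1.04).

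**The case against.** The strongest reply is that Table 2 lists outcomes and data sources and does not specify a model. Baseline HbA1c is not in its covariate row, yet section {20a} plans to adjust for it, so absence from the row does not exclude a variable. The primary regression's baseline characteristics are not enumerated, the imputation variables are examples of predictors of missingness and outcome, and a full covariate list is commonly left to the statistical analysis plan. The regression and the weighting could also deal with chance imbalance at the second stage. All of this stands. A reader might infer that the analysis ignores its own design; the documents do not support that, because nothing in them keeps site out of the regression or the imputation.

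What the reply does not reach is the comparison of the six conditions. One-way ANOVA with Tukey tests is a stated choice of method and by construction has no site term, whatever the analysis plan adds elsewhere. The lists that are given also name several covariates and pass over the one variable used to stratify.

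A reader might also treat diabetes type as an equal omission. It is only an eligibility characteristic and does not enter either randomisation, so leaving it out can cost precision or imputation quality but does not depart from the design. Finally, the gains above do not allow for overlap with baseline HbA1c, race/ethnicity or insurance, which could make them smaller.

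**Conclusion.** The point holds as a modest matter of precision and clarity. Site stratifies the first randomisation, is not among the named covariates or imputation variables, and cannot enter the ANOVA/Tukey comparison. If the sites differ by 0.2 to 0.5 SD, naming it recovers about 1% to 6% of residual variance; if they hardly differ, the gain is negligible. That range is an assumption, since the documents give no site effect.

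A reader might infer that omission inflates type I error or undermines the sample size. Neither follows. The first-stage test is at most mildly conservative (about 4.9% to 4.3% under the same assumption), the simulated six-condition rate without site was 0.045 to 0.053, and 216/270 is reproduced and need not change.

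**What to change.** 1. Name recruitment site as a fixed effect in the primary and secondary outcome models and in the imputation model.
2. List site among the variables in the dataset sent to the blinded statistician, as a separate field, since the substituted identifier does not carry it.
3. Take the overall test and the Tukey-adjusted pairwise contrasts from the linear model adjusted for baseline HbA1c and site, in place of the unadjusted one-way ANOVA.
4. Optionally, add diabetes type (1 or 2), known from screening, as a prognostic covariate, stating that it is there for precision only.

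The cost is one degree of freedom for site, two with diabetes type, plus wording. No new data are needed: the study team already records site at enrolment. The choice should be fixed before the treatment codes are revealed, so that covariates are not selected after the results are seen.

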### Participant timeline {13}

See Fig. 3*. Schedule of enrollment, interventions, and assessments* for the full participant timeline.

**Fig. 3 Fig3:**
[figure not shown]
Schedule of enrollment, interventions, and assessments

### Sample size {14}

The sample size calculation, performed using G*Power (version 3.1), is based on the primary outcome of HbA1c over the 12-month study period, with the primary predictor being the six treatment conditions taken over the course of the study. The Null (H0) and Alternative (H1) Hypotheses are H0: There is no difference in the mean change in HbA1c among the six treatment groups, and H1: There is a significant difference in the mean change in HbA1c among the six treatment groups. The analysis assumes a significance level of 5%, 80% power, six treatment groups, equal group allocation, and a medium effect size of *f* = 0.25. The effect size of *f* = 0.25 was selected based on Cohen’s conventions for effect sizes in behavioral sciences, where 0.10 represents a small effect, 0.25 represents a medium effect, and 0.40 represents a large effect. A medium effect size is considered appropriate for this study, as it balances the detection of meaningful clinical differences with practical sample size considerations. Previous studies on diabetes management interventions such as DSMT and RGM have reported effect sizes in this range, indicating that a medium effect size is a reasonable expectation for interventions aimed at reducing HbA1c [13, 25].

The sample size estimation properly accounted for the multiple groups and comparisons inherent in the SMART design. Specifically, we conducted the sample size estimation for detecting a difference in HbA1c change across the six treatment groups, using an ANOVA framework, which inherently accounts for multiple comparisons. To ensure robustness and accommodate potential dropouts, we inflated the sample size by 20%. Thus, the minimum required sample size is 216 patients, and to account for an anticipated dropout rate, we aim to recruit 270 patients. This approach ensures that the study is adequately powered to detect significant differences across all treatment conditions, providing a solid basis for our subsequent analyses.

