Randomization envelopes were created for the second round of randomization at 6 months following a similar protocol. In this case, the staff member printed 60 pieces of paper that say “CHW,” 60 pieces of paper that say “RGM,” 60 pieces of paper that said DSMT, and 60 pieces of paper that say “CHW + RGM.” We assumed that a certain number of participants would improve by at least one percentage point and would not be randomized. After creating the 240 envelopes, the staff member created two boxes of envelopes, stratified by the initial treatment assignment. In the first box, for participants initially assigned to DSMT, the staff member shuffled and placed the CHW and RGM envelopes in the box marked “DSMT.” In the second box, for participants initially assigned to RGM, the staff member shuffled and placed the remaining DSMT and CHW + RGM envelopes in the box marked “RGM.”

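### The 216/270 sample size gives 80% power for one omnibus F test on six equal paths, not for the pairwise path comparisons the protocol says it covers

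*Protocol article*

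**What the plan says.** The Sample size section of the protocol article tests one global null: "There is no difference in the mean change in HbA1c among the six treatment groups". Its inputs are a 5% level, 80% power, "six treatment groups, equal group allocation, and a medium effect size" of f = 0.25, taken from Cohen's conventions. From these, "the minimum required sample size is 216 patients, and to account for an anticipated dropout rate, we aim to recruit 270 patients".

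The section then makes two broader statements. It says that the multiple groups and comparisons of the SMART are covered by "using an ANOVA framework, which inherently accounts for multiple comparisons". It closes with "This approach ensures that the study is adequately powered to detect significant differences across all treatment conditions".

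Three other places bear on this:

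- Statistical methods (Primary outcomes) follows the one-way ANOVA of the six conditions with Tukey pairwise tests, or Dunn tests with Hommel correction if the data are not normal.
- Trial design states one directional hypothesis: path E (DSMT, then CHW) will show the largest HbA1c reduction of all the paths.
- Trial design and Intervention description keep 6-month responders in their first arm and rerandomise only non-responders. On how many will respond, Sequence generation says only: "We assumed that a certain number of participants would improve by at least one percentage point and would not be randomized".

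**The concern.** An omnibus F test controls the error of one global test and has power for one global alternative. Rejecting it does not show which paths differ, and 80% power for it does not carry over to the 15 pairs among six paths. The Tukey correction in the analysis section would be unnecessary if the ANOVA framework already dealt with multiple comparisons.

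The equal-allocation input also sits badly with the design. The sizes of the six paths are set by how many participants respond at 6 months, not by an allocation ratio.

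Interpretation is at stake. A reader who accepts the power statement would take a non-significant difference between two paths, including one involving path E, as evidence of no difference. The trial may have had less than an even chance of detecting it.

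**Working it through.** **Inputs from the Sample size section:** alpha 0.05, six equal groups, f = 0.25, 216 evaluable, 20% dropout. No SD of HbA1c change is given, so differences d are in SD units. Response rates and patterns of means are my assumptions, shown as ranges.

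**Step 1. Reproduce the plan's figure.** The noncentrality is λ = N·f² with 5 and N − 6 df.
- N = 216: λ = 216 × 0.0625 = 13.5, power 0.811.
- N = 210: power 0.798.
- The smallest N reaching 80% is 211, which rounds up to six groups of 36, so 216.
- Dropout: 216 / (1 − 0.20) = 270.

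Both figures are correct.

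**Step 2. Tukey power at the same f, 36 per path.** The critical value is q(0.95; 6, 210)/√2 = 2.876. Pair power comes from the noncentral t with 210 df and noncentrality d·√(36/2) = 4.243·d.

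| Pattern of means giving f = 0.25 | Largest d | Noncentrality | Tukey power |
|---|---|---|---|
| Three v three | 2f = 0.50 | 2.12 | 23% |
| One path differs from five | 6f/√5 = 0.67 | 2.85 | 49% |
| Equally spaced (range) | 0.73 | 3.11 | 59% |
| Two extremes, four in the middle | f·√12 = 0.87 | 3.67 | 79% |

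For 80% Tukey power at 36 per path, d must be about 0.88. If all 270 were evaluable (45 per path), the four powers would be 31%, 62%, 73% and 89%.

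**Step 3. Path E against every other path.** Suppose only path E differs (d = 0.67). By simulation (40,000 runs), all five Tukey comparisons favour E significantly in about 16% of trials.

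**Step 4. The equal-allocation input.** With response rate r in both arms and 216 evaluable, each of the two responder paths holds 216·r/2 = 108r. Each of the four rerandomised paths holds 216·(1 − r)/4 = 54(1 − r). These are equal only when 108r = 54(1 − r), so r = 1/3.

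If one path of size n differs by d = 0.67 (d² = 0.45), then λ = 0.45·n·(1 − n/216).

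| Assumed response | Responder path n | Rerandomised path n | Omnibus power, only E differs | Omnibus power, only a responder path differs |
|---|---|---|---|---|
| 10% | 10.8 | 48.6 | 90% | 33% |
| 20% | 21.6 | 43.2 | 87% | 60% |
| 33% | 36 | 36 | 81% | 81% |
| 50% | 54 | 27 | 70% | 92% |
| 70% | 75.6 | 16.2 | 47% | 97% |

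The joint result in Step 3 does not rise above about 16% at any rate checked.

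**Step 5. What 216 completers detect with 80% power** (two-sided 5%, unadjusted for covariates; (1.96 + 0.84)² ≈ 7.85; response 10% to 33%):
- First stage, DSMT v RGM, 108 v 108: √(2 × 7.85/108) = 0.38 SD (does not depend on r).
- Two embedded regimens with different first stages: √(4 × 7.85 × (2 − r)/216) = 0.53 SD at 10%, 0.51 at 20% and 0.49 at 33%. With Bonferroni for six pairs, the range is 0.61 to 0.65 SD.
- Second-stage contrast within one first-stage arm, 54(1 − r) per option: √(2 × 7.85/48.6) = 0.57 SD at 10% and √(2 × 7.85/36) = 0.66 SD at 33%.

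**The case against.** The best defence is that the stated hypotheses are omnibus, the calculation for them is right, and pairwise type I error is controlled by Tukey or Hommel. All of that stands. It answers a different question, because controlling false positives does not supply power.

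The planned regression adjusts for covariates, and these figures are unadjusted. If covariates explained 30% of the variance (an assumption), the 49% would become about 70%, still short of 80%. The Secondary outcomes text concedes limited power from adding the CHW, but only for exploratory analysis, so it does not correct the Sample size section.

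Several stronger readings are tempting, and the document does not support them:

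- A reader might infer an arithmetic error in 216 or 270. There is none.
- A reader might treat the 16% as the trial's power for its main question. The plan states an expectation that E will be largest. It does not require E to beat all five paths jointly.
- A reader might infer from the 240 second-stage envelopes that only 11% to 20% responders were expected. The stock caps the number of non-responders: (270 − 240)/270 = 11% is roughly a minimum response rate if nobody drops out. It is compatible with one third.
- A reader might conclude that the design cannot give equal paths, or that imbalance always costs power. Equal paths arise at one-third response, and omnibus power for a path E effect rises to 87–90% at 10–20% response.

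**Conclusion.** The two statements in the Sample size section are wrong as written. The 80% applies to one omnibus test under equal path sizes. At the protocol's own effect size, the best-placed pair has Tukey power between 23% and 79%, so no pattern examined reaches 80% with 216 evaluable.

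This conclusion holds even with perfectly equal paths. The unstated response rate adds uncertainty in both directions rather than a uniform loss: from 90% down to 47%, or from 33% up to 97%, depending on which path differs.

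The pairwise figures rest on a common SD, no covariate adjustment and the four mean patterns shown. The response-rate figures also assume the same rate in both first-stage arms and 216 evaluable.

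**What to change.** In the Sample size section, keep 270 and change the text:

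1. Delete the statement that the ANOVA framework takes care of multiple comparisons, and the statement of adequate power across all conditions.
2. Say that 216 evaluable gives 80% power for the omnibus test at f = 0.25 if the six paths are equal in size.
3. State the assumed 6-month response rate and the path sizes it implies.
4. Report Tukey pairwise power, noting that 80% needs about d = 0.88 at 36 per path.
5. Add what 216 completers detect with 80% power, unadjusted: about 0.38 SD for first-stage DSMT v RGM; 0.49–0.53 SD for regimens with different first stages (0.61–0.65 SD with Bonferroni for six pairs); and 0.57–0.66 SD for the second-stage contrast within one arm. The regimen and second-stage ranges are for 10–33% response.

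This needs no change to recruitment, randomisation or the planned analyses. The cost is that the power the protocol can claim becomes less favourable.
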